#### 2.2.7. Analysis Plan

Distributions of the population characteristics at baseline will be examined by medians, percentiles, and proportions. All percentiles and proportions will be reported in line with national data protection rules, which require that estimates be based on data from at least five individuals [28].

G-computation will be used to estimate the causal effect on 20-year outcomes, comparing the increase-or-no-true-reduction group against the true-reduction group in the primary analysis, and against the reduction group split by the median into lower and higher reduction in the secondary analysis. We will interpret results by evaluating the magnitude, direction, and precision of effect estimates rather than relying solely on binary significance testing, consistent with recommendations from authoritative sources [29]. The outcome model will include baseline covariates as well as time-varying covariates described in the 2.2.6 assumption paragraph. Predicted potential outcomes under each intervention strategy will be generated from the fitted model, and standardized estimates of the mean potential outcomes for each group will be obtained. Average treatment effect will be estimated, and 95% confidence intervals computed via the delta method using the “marginaleffects” package [30] in R 4.5.3.

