## 2. Materials and Methods

In this target trial, the population of interest comprises adults, 20 years or older, with no history of cardiometabolic disease who would be randomized to receive PFAS-reducing counseling or no counseling, with adherence evaluated after 10 years to allow sufficient time for natural PFAS elimination and isolate the effect of the PFAS-reducing counseling from residual baseline PFAS levels. Serum lipids would be assessed 20 years post-baseline. We will emulate the target trial using the CCHS cohort by applying identical eligibility criteria and further restricting the cohort to individuals who participated in both the follow-up and outcome assessment visits. Reduced exposure to and increased elimination of PFAS can be achieved through individual PFAS-reducing counseling focused on dietary and lifestyle changes and PFAS awareness [21,22,23]. Since no counseling intervention was conducted in the CCHS, the intervention assignment in the emulation is inferred from changes in serum PFAS concentrations between baseline and follow-up visit, a period during which PFAS is expected to decrease uniformly across our population due to regulatory changes. The emulation therefore relies on an as-treated approach, assuming covariate-adjusted exchangeability, with outcomes assessed 20 years after baseline. In the following, we specify the target trial and target trial emulation according to the Transparent Reporting of Observational Studies Emulating a Target Trial (TARGET) [24]. Table 1 summarizes the target trial and emulation.

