#### 2.1.3. Outcome and Follow-Up Period

Outcomes of interest are serum lipid biomarkers including total cholesterol, LDL cholesterol, high-density lipoprotein (HDL) cholesterol, remnant cholesterol, and triglycerides. Follow-up would start at assignment to an intervention strategy at baseline. Loss to follow-up would include nonparticipation in the 20-year outcome biomarker assessment visit, emigration, withdrawal from the study or revocation of consent, or death. Adherence would be evaluated through telephone interview 10 years after intervention assignment. To isolate the effect of PFAS-reducing counseling from residual baseline PFAS levels, it is necessary to allow sufficient time for natural PFAS elimination to occur. For example, Perfluorohexanesulfonic acid (PFHxS) has an estimated biological half-life of approximately 5.3 years [25]. This implies that roughly 75% of baseline serum PFHxS would be naturally eliminated after two half-lives, with even greater elimination expected for the other PFAS with shorter half-lives. To obtain optimal temporal separation between adherence and the outcome, we would wait 10 years to capture long-term effects, effectively separating past exposure from current effects. The temporal structure of the target trial is presented in Figure 1.

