#### 2.2.3. Intervention Strategies and Assignment

Because no formal PFAS counseling intervention was provided in the CCHS, intervention assignment will be inferred from the observed change in serum PFAS concentrations between the baseline and follow-up visit. The change in each individual PFAS will be analyzed separately. Lower decreases in serum PFAS levels can result from routine laboratory measurement error (assay coefficient of variation, CV) rather than a true physiological change. To avoid misclassifying analytical noise as a genuine decrease, we applied a reference-change-value approach adapted from Harris and Yasaka’s framework [27]. In the primary analysis, for each participant, the laboratory-reported analytical CVs for baseline and follow-up PFAS measurements will be combined, yielding a participant-specific threshold that reflects the total measurement error expected for that individual. Increases or reductions at or below this threshold will be categorized as “increase/no true reduction”; reductions exceeding it will be categorized as “reduction”, representing a true decrease beyond measurement variability. In the secondary analysis, we will divide the “reduction” group by the median to separate lower and higher reductions. This classification aligns with an as-treated analysis, in which participants are analyzed according to their observed exposure change rather than a randomized assignment.

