## 4. Methodological Considerations

In an attempt to move beyond conventional exposure-outcome analyses, we explicitly followed the TARGET Statement [24] to articulate a well-defined causal question and to align eligibility criteria, intervention strategies based on observed reduction in PFAS, outcome timing, follow-up, and causal contrasts with a hypothetical PFAS counseling trial. This framework allowed us to transparently document the design choices and assumptions required to emulate such a trial using long-term data from the CCHS.

The CCHS will allow us to leverage temporally separated measurements of PFAS concentrations, with the serum lipids outcome assessed at a subsequent visit, thereby ensuring temporality between exposure and outcome. The 10-year interval between PFAS measurements improves the ability to distinguish new exposure from residual baseline levels. Consequently, the change between the two PFAS measurements more strongly reflects PFAS exposure during the follow-up period and is therefore more informative for evaluating the causal relationship with lipid levels measured 10 years later. In addition, the study will benefit from rich longitudinal covariate information collected through questionnaires and clinical examinations from the CCHS, as well as from national registries, which will support the exchangeability assumption through adjustment for all identified confounders. We will also capture a period during which PFAS exposures in the general population are expected to have declined following regulatory changes, with some compounds showing steeper decreases than others [31].

Serum lipid concentrations were measured in the non-fasting state in the CCHS, consistent with current Danish and broader European laboratory practice. Non-fasting blood sampling does not affect cholesterol, which differs minimally between fasting and non-fasting states [32]. However, triglycerides are known to rise postprandially; therefore, non-fasting measurements introduce additional within-person variability related to unmeasured time since last meal [32]. Because fasting status was uniform across the cohort and unrelated to exposure status, this measurement variability is expected to be non-differential with respect to exposure and to attenuate precision rather than bias the estimated effect.

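### The delta-method intervals name no robust variance; with a homoscedastic model covariance they would miscover if the exposure groups differ in both size and residual variance (minor)

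*Protocol article*

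**What the plan says.** Section 2.2.7 (Analysis Plan) sets out the emulation analysis as g-computation, "comparing the increase-or-no-true-reduction group against the true-reduction group in the primary analysis". "Predicted potential outcomes under each intervention strategy will be generated from the fitted model", the predictions are standardised, and the average effect is reported with "95% confidence intervals computed via the delta method" in a named R package. No residual-variance assumption, robust variance or bootstrap is mentioned. The same section says that results will be judged by size, sign and precision and not by significance alone.

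No section gives expected group sizes or lipid SDs by group. Four places bear on the likely split:

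- Section 2 calls the interval between baseline and follow-up "a period during which PFAS is expected to decrease uniformly across our population due to regulatory changes".
- Section 2.1.3 says that "roughly 75% of baseline serum PFHxS would be naturally eliminated after two half-lives".
- Section 2.2.3 sets the cut between groups at assay error: "the laboratory-reported analytical CVs for baseline and follow-up PFAS measurements will be combined", and any larger fall counts as a reduction. Each PFAS is classified separately.
- Section 4 qualifies the decline, "with some compounds showing steeper decreases than others".

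**The concern.** The delta method passes on whatever covariance it is given, so that matrix decides the interval width, and it is the one element of the interval method that section 2.2.7 leaves out. Carried out as written, the natural choice is the fitted model's own covariance. For a linear model this pools one residual variance over both groups, and the larger group dominates the pool. If the smaller group is more variable, its mean is less certain than the pooled variance implies and the interval is too narrow. If it is less variable, the interval is too wide.

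Precision is a stated basis for interpretation, and the same no-reduction group is the reference for the secondary analysis, so a misjudged variance would carry through both. The direction depends on which group is more variable, so a reader could not correct for it by eye.

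**Working it through.** **Plan figures.** The article states no figure for the lipid intervals. The analysed number reproduces from section 3: 2360 − 374 − 117 = 1869; 1869 − 728 − 304 = 837; 837 − 102 − 2 = 733; 733 − 38 = 695; 695 − 40 = 655. This matches the 655 in section 4. The only sample-size calculation (155 and 87 per group, section 4) concerns baseline PFAS in non-continuing participants and has no bearing here.

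**Is a small no-reduction group plausible?** The CVs and the multiplier applied to them are not given. Assuming CVs of 5–10% and a threshold of 1.96 × √2 × CV, the cut is a fall of about 14–28%. The article's own elimination figure for PFHxS is roughly 75% over two half-lives, and it expects more for compounds with shorter half-lives. Continued intake offsets part of this, and declines differ by compound. A small no-reduction group is therefore a fair inference for some PFAS, not for all.

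**Formula.** Let n₁, s₁ be the size and residual SD of the smaller group, n₂, s₂ those of the larger, and N = 655.

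- Pooled variance of the difference: [(n₁s₁² + n₂s₂²)/N] × (1/n₁ + 1/n₂)
- True variance: s₁²/n₁ + s₂²/n₂
- k = √(pooled/true); coverage = 2Φ(1.96k) − 1

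**Worked case** (assumed 10% share, SD ratio 1.5): n₁ = 65.5, n₂ = 589.5, s₁² = 2.25, s₂² = 1.

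- Pooled = 1.125 × 0.01696 = 0.01908
- True = 0.03435 + 0.00170 = 0.03605
- k = √(0.01908/0.03605) = 0.73; coverage 84.6%

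**Results** (k, then coverage). Shares and SD ratios (smaller/larger group) are all assumptions.

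| Smaller group | SD ratio 0.75 | 1.0 | 1.2 | 1.33 | 1.5 |
|---|---|---|---|---|---|
| 50% (328) | 1.00, 95.0% | 1.00, 95.0% | 1.00, 95.0% | 1.00, 95.0% | 1.00, 95.0% |
| 20% (131) | 1.18, 98.0% | 1.00, 95.0% | 0.90, 92.1% | 0.85, 90.2% | 0.79, 87.9% |
| 10% (66) | 1.26, 98.6% | 1.00, 95.0% | 0.86, 91.0% | 0.80, 88.2% | 0.73, 84.6% |
| 5% (33) | 1.29, 98.9% | 1.00, 95.0% | 0.85, 90.4% | 0.77, 87.1% | 0.70, 82.8% |

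The column at 1.0 and the row at 50% show that both kinds of inequality are needed.

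**Simulation of the remedy.** With 4000 runs per scenario, a linear model, 25 covariates, normal errors, shares of 5–50% and SD ratios of 0.75–1.5:

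- model-based coverage 82.5–98.7%
- HC0 coverage 92.6–94.5%
- HC3 coverage 94.6–95.6%

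At equal SDs the mean HC3 standard error was 0.135 against 0.132 at a 10% share, and 0.188 against 0.182 at 5%, that is, 2–3% larger.

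With lognormal errors (log-SD 0.5, one covariate, 2000 runs), HC3 covered 94–96% at a 10% share and 92–94% at 5%. A further simulation under a null effect, with group membership depending on covariates and outcome spread rising with the mean, gave 88–93% for the model-based covariance and 93–95% for HC3.

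**The case against.** The strongest reply is that section 2.2.7 contains no wrong statement. A reader might infer that the delta method itself assumes equal variances. It does not, and the article never says that a model-based covariance will be used. Nor does it give the family or scale of the emulation's outcome model: linear regression is named only for the hypothetical trial's intention-to-treat analysis in section 2.1.6. An article may leave the covariance estimator to a fuller plan. All of this stands, and it makes the point conditional.

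A reader might also infer that the plan expects very unequal groups. It expects a general decline, gives no shares, and says that compounds differ. The imbalance is an implication only.

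Unequal variance is the weakest link. Section 4 says that "non-fasting measurements introduce additional within-person variability related to unmeasured time since last meal", but goes on to expect this to be unrelated to exposure, so that passage is not evidence of different spread by group. If SD were proportional to the mean, a ratio of 1.5 would need a mean 50% higher in the smaller group, and 1.2 would need 20%; nothing in the article supports either. The documents therefore do not support a claim that every PFAS–lipid interval is wrong.

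What survives is plausibility. If triglycerides are skewed with spread that rises with the mean (an assumption), any difference in group make-up brings a difference in variance. Remnant cholesterol, obtained by subtraction using a calculated LDL (section 2.2.4), would share in it. Lipid-lowering medication started after baseline is said in section 2.2.8 to affect lipids but is not among the covariates in section 2.2.6, so the groups may mix treated and untreated people in different proportions. The article gives no ground for one common residual variance across five lipids and every PFAS analysed.

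**Conclusion.** The point holds in conditional form, as minor. If a homoscedastic model covariance enters the delta method, and the groups differ in both size and residual variance, nominal 95% intervals cover about 83–99% over assumed shares of 5–20% and SD ratios of 0.75–1.5. At the milder ratio of 1.2 they cover 90–92%. With equal variances or equal groups there is no loss. The direction is unknown in advance, and the article supplies neither the shares nor the SDs. Because HC3 costs almost nothing when variances are equal and restores most of the coverage when they are not, it is the better choice to fix before group sizes are seen.

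**What to change.** In section 2.2.7, state that the delta method will use a heteroscedasticity-consistent (HC3) covariance of the outcome model for all lipid outcomes, in the primary and secondary analyses. If a fuller analysis plan already names an estimator, the article need only agree with it. HC3 is preferable to HC0 here because HC0 under-covered slightly in the simulations.

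The cost is one phrase. Standard errors become slightly noisier, and with skewed outcomes coverage is still mildly low, about 92–94%, when the smaller group is about 30. Reporting the size of each group beside each interval would let readers see where that applies.

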#### 2.2.8. Sensitivity Analysis

First, because initiating lipid-lowering medication after baseline influences serum lipid outcomes, we will perform a sensitivity analysis in which time-varying lipid-lowering medication use is set to zero. With this, we will simulate a counterfactual scenario in which no participant initiated treatment during follow-up, allowing us to assess how post-baseline lipid-lowering medication uptake influences our effect estimates. Second, to evaluate the implications of using alternative exposure definitions applied in prior PFAS studies, we will estimate the associations between (i) baseline PFAS concentrations and serum lipid levels at the follow-up and outcome assessment visits and (ii) follow-up PFAS concentrations and lipid outcomes at the outcome assessment visit. If estimates obtained using these alternative single time-point exposure definitions differ from those derived from the target trial emulation, such discrepancies would indicate that the conventional observational approach, even when temporality is respected, may still produce biased effect estimates.

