The emulation conditions require continuous participation across all three visits as well as available serum for PFAS measurement and serum lipid data. If continuous participation is partly related to underlying health status and PFAS simultaneously influence this through their effect on health, this could lead to selection bias. Although inverse probability weighing could address this form of administrative selection, it would require costly PFAS quantification in participants with incomplete follow-up to construct censoring models. This presents a bias-variance tradeoff where the reduction in bias is outweighed by the loss of statistical precision and increased estimator variance. Given these constraints, the design choice of the emulation differs from the target trial and limits our ability to fully emulate the trial’s follow-up process. PFAS was not part of the original scope nor measured during active data collection in the CCHS, and participants were unaware of their PFAS levels at that time (PFAS will be measured from stored blood samples), minimizing the risk of self-selection due to PFAS. As illustrated by the selection-bias DAG (Figure 6), conditioning on participation may introduce selection bias, potentially inducing an association between PFAS changes and serum lipid outcomes even in the absence of a true causal effect. If participants with increases in PFAS concentrations remain in the study, they are more likely to represent a “healthier subset” with more favorable serum lipid profiles compared to the target population, potentially leading to an underestimation of the true effect of PFAS reduction. Accordingly, estimates should be interpreted as conditional on continuous study participation and may not be fully generalizable to the original target population. To assess the magnitude of this selection, we consider comparing baseline PFAS concentrations between individuals in the study population and a random sample of those who participated only at baseline, as well as at baseline and at follow-up, to get an indication of how strongly PFAS is associated with continuous participation. Based on an expected study population of 655, we would need to measure baseline PFAS for 155 individuals in each group to be able to detect a standardized mean difference in Cohen’s d = 0.25 (one-fourth of a standard deviation) using a two-sided alpha of 0.05 and 80% power. A minimum of 87 individuals would need to be measured to ensure detection of a difference no larger than Cohen’s d = 0.32 (one-third of a standard deviation). However, because PFAS testing is expensive, analyzing the samples from these additional individuals is an optional secondary analysis that will only be conducted if additional funding is secured.

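### The second sensitivity analysis offers bias in the conventional approach as the only reading of a discrepancy, although the analyses target different quantities and can differ without bias

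*Protocol article*

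**What the plan says.** Section 2.2.8 gives the purpose of the second sensitivity analysis as "to evaluate the implications of using alternative exposure definitions applied in prior PFAS studies". There are two comparators. The first relates "baseline PFAS concentrations and serum lipid levels at the follow-up and outcome assessment visits"; the second relates "follow-up PFAS concentrations and lipid outcomes at the outcome assessment visit". If either differs from the emulation, then "such discrepancies would indicate that the conventional observational approach, even when temporality is respected, may still produce biased effect estimates". No other explanation is mentioned there.

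The emulation estimate is of another kind. Under 2.2.3, "intervention assignment will be inferred from the observed change in serum PFAS concentrations between the baseline and follow-up visit", and a reduction must exceed a threshold for analytical error. Under 2.2.7 the effect is a g-computed mean difference, "comparing the increase-or-no-true-reduction group against the true-reduction group in the primary analysis".

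Section 4 discusses weaknesses of the emulation. Conditioning on participation is described as "potentially inducing an association between PFAS changes and serum lipid outcomes even in the absence of a true causal effect", with underestimation as the expected direction. Concurrent lifestyle change is said to risk overestimation.

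**The concern.** Two estimates can be compared for bias only if they aim at the same quantity. Here one is a difference between two change groups and the others are associations with a level. The first comparator also has a part whose outcome is measured at the follow-up visit, about 10 years before the emulation's outcome. The article itself holds that the exposures carry different information: the Introduction says that a single time point cannot separate current exposure from existing body burden, and section 4 says that "the change between the two PFAS measurements more strongly reflects PFAS exposure during the follow-up period". Disagreement between such quantities is not in itself evidence that one of them is biased.

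The attribution also runs one way. A discrepancy is read as a possible fault of the conventional approach, with no mention in 2.2.8 that it might come from the emulation or from chance.

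The primary lipid estimate is not at stake. The methodological message is: section 5 presents the work as showing how target trial emulation can strengthen causal inference, and this comparison is the only planned empirical check of the emulation against conventional exposure definitions.

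**Working it through.** The article states no figure for this comparison, so there is nothing to reproduce. The check has two parts.

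**1. The analyses side by side**

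| | Exposure | Outcome visit | Contrast |
|---|---|---|---|
| Emulation (2.2.3, 2.2.7) | Change from baseline to follow-up, in two groups | Outcome assessment | Mean difference, reduction vs none |
| Comparator (i) (2.2.8) | Baseline concentration | Follow-up and outcome assessment | Association with level |
| Comparator (ii) (2.2.8) | Follow-up concentration | Outcome assessment | Association with level |

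Exposure and contrast differ in every row, and part of comparator (i) also differs in outcome visit.

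**2. Can the estimates differ when nothing is biased?**

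All inputs in model A are assumptions for illustration; none comes from the article.

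*Model A.* There is no confounding, selection or measurement error. Baseline log PFAS has a geometric SD of 1.8. Follow-up log PFAS = log(0.5) + 0.7 × baseline log PFAS + noise, which is a 50% median decline. Lipid = 0.2 × follow-up log PFAS + error. A reduction is a fall of more than 20%.

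- Follow-up level: 0.2 per log unit, by construction.
- Baseline level: 0.2 × 0.7 = 0.14 per log unit.
- Reduction vs none, adjusted for baseline: 0.2 × the adjusted difference in follow-up log PFAS between the groups. That difference depends on the noise SD.

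| Noise SD (log scale) | Adjusted difference in follow-up log PFAS | Reduction contrast (× 0.2) |
|---|---|---|
| 0.2 | -0.37 | -0.07 |
| 0.4 | -0.73 | -0.15 |
| 0.6 | -1.03 | -0.21 |
| 0.8 | -1.34 | -0.27 |

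The differences come from simulation (2,000,000 people, linear baseline adjustment). Each estimate is correct for its own quantity. The contrast varies almost fourfold while the two slopes stay at 0.20 and 0.14.

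*Model B.* This one uses the half-life of 5.3 years quoted in 2.1.3. The fraction remaining after 10 years is 2^(-10/5.3) = 0.27, so follow-up PFAS = 0.27 × baseline + new inflow. Assumed: lognormal baseline and inflow, an analytical CV of 5%, a threshold of 1.96 × √2 × 5% = 13.9%, a true effect of 0.1 mmol/L per PFAS unit, and again no bias.

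| Lipids driven by | Reduction contrast, baseline-adjusted | Baseline level, per unit (per SD) | Follow-up level, per unit (per SD) |
|---|---|---|---|
| Follow-up burden | -0.049 | +0.027 (0.016) | +0.100 (0.032) |
| Mean of both burdens | -0.025 | +0.064 (0.039) | +0.098 (0.032) |
| No PFAS effect | about 0 | about 0 | about 0 |

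Scaling per SD does not make the two level estimates equal, and their order reverses with the assumed mechanism. With no PFAS effect and no bias, all three agree at zero.

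Both models assume adjustment for baseline PFAS, which 2.2.6 makes conditional on its correlation with the change.

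**The case against.** The strongest defence is that the sentence is hedged: it says the conventional approach may be biased. A reader might infer that the article treats every discrepancy as proof of bias, or that the methodological conclusion is settled in advance. The text supports neither. The hedge is there, and under a null PFAS effect without bias all the analyses would agree. Whether PFAS has an effect is the study question.

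Second, 2.2.7 says that results are read by magnitude, direction and precision. In both illustrations the directions are concordant: higher levels go with higher lipids, and reduction with lower lipids. The opposite sign is only coding. A careful analyst could call such results consistent. That stands, but 2.2.8 does not say that discrepancy means discordant direction, and differences in magnitude remain open to the stated reading.

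Third, section 4 discusses the emulation's own biases at length, so it would be wrong to say that the article treats the emulation as beyond doubt. Selection and unmeasured diet could also affect single-visit analyses in the same people, and a bias shared equally would not explain a difference. This tempers the point. However, nothing in the article shows that these biases act equally on a change category and on a level, and 2.2.8 does not carry the caveats over.

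Fourth, the covariate set and the interval method for a sensitivity analysis are details that an article may leave to the analysis plan. Their absence is not part of this point. The stated purpose of the analysis is already close to what is needed, and both comparators include the outcome assessment visit.

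**Conclusion.** The point holds as a defect of interpretation. Section 2.2.8 offers one explanation for a discrepancy when at least three others are open: different target quantities, sampling error in about 655 people (695 - 40), and bias in the emulation that section 4 admits.

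The size is illustrative. Under model A the bias-free estimates are +0.20, +0.14 and -0.07 to -0.27; the range comes from the noise SD, which the article does not give. That the quantities can differ without bias does not depend on these particular inputs, but it does require a non-null PFAS effect. The primary estimate, sample and measurements are unaffected.

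**What to change.** Replace the last sentence of 2.2.8 with a statement that a difference between the single-visit analyses and the emulation shows sensitivity to the exposure definition and does not by itself identify which estimate is biased.

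If the comparison is meant to bear on bias, limit it to lipids at the outcome assessment visit. Use the same people and covariates, express all estimates on one contrast scale (for example, a g-computed difference per halving of PFAS), and report an interval for the difference that allows for the shared participants. A paired bootstrap would do this. The follow-up-visit outcome in comparator (i) can stay as a descriptive result.

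The cost is a weaker methodological claim and a little more analysis work. No new PFAS assays are required.
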